## Abstract

For deep partial-thickness burns no consensus on the optimal treatment has been reached due to conflicting study outcomes with low quality evidence. Treatment options in high- and middle-income countries include conservative treatment with delayed excision and grafting if needed; and early excision and grafting. The majority of timing of surgery studies focus on survival rather than on quality of life. This study protocol describes a study that aims to compare long-term scar quality, clinical outcomes, and patient-reported outcomes between the treatment options. A multicentre prospective study will be conducted in the three Dutch burn centres (Rotterdam, Beverwijk, and Groningen). All adult patients with acute deep-partial thickness burns, based on healing potential with Laser Doppler Imaging, are eligible for inclusion. During a nine-month baseline period, standard practice will be monitored. This includes conservative treatment with dressings and topical agents, and excision and grafting of residual defects if needed 14–21 days post-burn. The subsequent nine months, early surgery is advocated, involving excision and grafting in the first week to ten days post-burn. The primary outcome compared between the two groups is long-term scar quality assessed by the Patient and Observer Scar Assessment Scale 3.0 twelve months after discharge. Secondary outcomes include clinical outcomes and patient-reported outcomes like quality of life and return to work. The aim of the study is to assess long-term scar quality in deep partial-thickness burns after conservative treatment with delayed excision and grafting if needed, compared to early excision and grafting. Adding to the ongoing debate on the optimal treatment of these burns. The broad range of studied outcomes will be used for the development of a decision aid for deep partial-thickness burns, to fully inform patients at the point of consent to surgery and support optimal person-centred care.

## Introduction

Burns are one of the most common types of trauma worldwide, causing significant disability [1, 2]. Today, acute burn care in high- and middle-income countries has improved to the point where the focus has shifted from survival as main outcome to outcomes like quality of life, leaving room to broaden our view to other challenges [3]. One of these challenges is the timing of surgery. The severity of a burn, determined primarily by total body surface area (TBSA) and depth of the injury, influences reparative healing potential, and is a primary indicator of the need for surgery [4–6]. For deep partial-thickness burns, currently no consensus regarding the optimal treatment has been reached, which remains a topic of debate [7]. Contrary to superficial partial-thickness burns and full-thickness burns, where the optimal treatment is evident. Superficial partial-thickness burns affect the epidermal and upper dermal layers of the skin, heal within 14 days and do not require surgery [8]. Full-thickness burns fully penetrate all layers of the skin into the subcutis. No spontaneous healing is expected and excision and grafting are always indicated [8–11].

The healing potential of deep partial-thickness burns varies with the longer time to healing being associated with increased scar risk. Two main treatment strategies are currently applied in high- and middle-income countries: 1) conservative treatment with delayed excision and grafting if needed; 2) early excision and grafting. Conservative treatment involves applying dressings and topical antimicrobial and antiseptic agents to the burn, after which spontaneous healing is awaited. If the remaining defects do not heal spontaneously within 14 to 21 days, the burn specialist can decide to perform excision and grafting. In case of early surgery, excision and grafting of the burn is performed within the first week to ten days post-burn [9].

Both treatment strategies have advantages and disadvantages. Early excision and grafting of deep partial-thickness burns is recommended by the International Society for Burn Injury for faster recovery, less pain, and possibly improved long-term scar outcomes [9]. Conservative treatment, on the other hand, avoids the mental and physical stress that can be associated with surgery, particularly for the frail or anxious patient [12]. Moreover, conservative treatment with dressings and antimicrobial agents does not involve donor site morbidity, which can result in pain, scarring, and long-term deviant pigmentation [13]. On the other hand, conservative treatment is associated with a longer time to re-epithelialisation and a prolonged length of hospital stay, which accounts for high costs in burn care [14, 15]. Also, it can be related to the development of hypertrophic scars and joint contractures due to delayed wound healing [14]. Additionally, early wound closure is associated with a reduced infection risk and shorter length of hospital stay, which can contribute to early rehabilitation [16, 17]. However, early excision and grafting might result in scarring of more superficially burned areas that might have been able to heal with little scarring if treated conservatively [3].

Two systematic reviews examined the evidence on the optimal treatment for deep partial-thickness burns. Ong et al. [14] included six randomized controlled trials on early versus delayed excision and grafting between 1966 and 2004. Timing of early excision ranged from less than 24 hours to 144 hours post-burn. Clinical outcomes such as mortality and blood loss were evaluated, and one of the included studies analysed cosmetics evaluated by healthcare professionals [18]. The systematic review concluded that early burn excision resulted in lower mortality and length of hospital stay, as well as increased blood transfusion requirements [14].

Miroshnychenko et al. [19] included nine randomized controlled trials comparing early burn surgery to late surgical intervention from 1982 to 2019. Early surgery was defined as excision and grafting within seven days post-burn, and delayed surgery as excision and grafting after seven days. The authors concluded that early excision and grafting may reduce length of hospital stay and mortality and might lead to better functional and cosmetic outcomes. However, the quality of evidence was low and outcomes varied between different studies [20, 21]. Again, the included studies primarily focused on clinical outcomes, and the only study that included scar quality found no statistically significant difference between both treatment groups [21].

The quality of evidence of the analysed studies in both systematic reviews is questionable. The majority of the studies date from the 1980s, which renders them outdated. Furthermore, the terms ‘excision’ and ‘excision and grafting’ seem to be used and analysed interchangeably. Therefore, this protocol describes the study that is designed to assess long-term scar quality of conservative treatment with delayed excision and grafting if needed, compared to early excision and grafting of deep partial-thickness burns in acute adult burn care. Thereby gaining more insight into the advantages and disadvantages of the treatment of these burns. In a multicentre prospective study, long-term scar quality of both treatment strategies will be analysed, and clinical and patient-reported outcomes will be examined.

## Materials and methods

### Study design

A multicentre prospective study with a 12-month follow-up period will be conducted in the three Dutch burn centres: Maasstad Hospital Rotterdam, Red Cross Hospital Beverwijk, and Martini Hospital Groningen. Patients with deep partial-thickness burns, scanned as yellow by Laser Doppler Imaging (LDI), will be monitored during 18 months; two nine-month periods with either therapy as the treatment of choice in one of the periods. This time period was chosen based on expected numbers and project logistics, such as staffing. Standard care in the Netherlands for deep partial-thickness burns is predominantly conservative treatment with delayed excision and grafting if needed. However, early excision and grafting is applied if deemed more appropriate for a specific patient. The first nine-month period (July 15^th^ 2022 to April 14^th^ 2023) this strategy is followed. In the following nine-month period (April 15^th^ 2023 to January 14^th^ 2024) clinical practice will be changed: early excision and grafting will be the primary treatment. However, in specific cases e.g. based on clinical expertise, conservative treatment can be applied. Depending on the received treatment, patients will be categorized as either the conservative treatment group with delayed excision and grafting if needed, or the early excision and grafting group.

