### Participants

#### Selection

Neither, randomisation nor blinding will take place. The used treatment strategy determines to which group the patient is assigned. The first group represents conservative treatment with delayed excision and grafting if needed, the second group represents early excision and grafting. If a patient is eligible for the study, a member of the research team will provide information about the study. The patient is asked for consent to take additional measurements 12 months after discharge. After reflection time and written informed consent, the patient is included.

Anyone using the protocol must consider the ethical implications of the timing of surgery in their own practice setting. To ensure patient safety, the attending physician is justified in deciding not to start or discontinue treatment from the allocated treatment, based on sound medical grounds and after consulting with the health care team. Deviation from the assigned treatment should be rare, and the reason must be thoroughly documented.

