#### Criteria

Adult (≥18 years) patients with acute thermal burns who are admitted for at least 24 hours or scheduled for surgery are eligible for this study, when the criteria listed below are met.

Inclusion criteria:

Burns with a size of >2.5 centimetres diameter;LDI scan indicating:
Deep partial-thickness burn: yellow wound area on LDI with healing potential between 14 and 21 days, or;Mixed superficial and deep partial-thickness burn: mixed red and yellow wound area on LDI, with a demarcated predominantly yellow area of at least 25cm^2^, or;Mixed full-thickness and deep partial-thickness burn: mixed blue and yellow wound area on LDI, with a demarcated predominantly yellow area of at least 25cm^2^.

The colour codes representing the perfusion units (PU) and healing potential are as follows [8, 23]:

Red/pink: PU 441–2500, healing potential within 14 days;Yellow/green: PU 201–440, healing potential about 14 to 21 days;Blue: PU 0–200, healing potential more than 21 days.

Exclusion criteria:

Frostbite injury [24];Burns suitable for primary closure;Patients unable to complete the Patient and Observer Scar Assessment Scale (POSAS) due to language restrictions or legal incompetence.

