### Primary outcome

#### Scar quality

The primary outcome measure of the study is long-term scar quality assessed with the POSAS (generic version, 3.0) 12 months after discharge. The POSAS is a widely used scar quality measurement instrument that comprises two separate scales: the Patient Scale and the Observer Scale [30]. The Patient Scale includes 17 questions about visual, tactile and sensory characteristics, and the overall opinion. The Observer Scale includes eight questions assessing the scar’s pigmentation, vascularity, surface level, surface texture, firmness, adherence, tension, and overall opinion. Each item is rated on a five-point scale. The lowest score is ‘1’, which corresponds to the situation of normal skin (i.e. normal pigmentation, no itching). Score ‘5’ equals the largest difference from normal skin (i.e. the worst imaginable scar or sensation) [30].

The Patient Scale is assessed by the patient, and two independent observers assess the Observer Scale on the study area(s). The assessment is mostly done during the standard 12-month outpatient appointment by the attending burn physician(s) and/or by members of the research team. If there is no standard 12-month outpatient appointment planned, the patient is invited to attend the clinic for the scar quality assessment, for which travel and parking expenses are reimbursed. All members of the research team and the burn physicians are trained to assess scar quality with the POSAS. Each burn centre’s highly experienced head of research provides a POSAS training on the latest version: POSAS 3.0 [30].

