### Secondary outcomes

#### Clinical outcomes

Time to wound healing of study area(s): this is defined as the number of days between burn injury and re-epithelialisation of >95% of the wound surface. Progression of re-epithelialisation is assessed by an experienced burn specialist and reported after every wound inspection.

Wound infection of study area(s): the attending physician will document whether a wound infection has occurred, based on inflammation characteristics (rubor, dolor, calor, tumor, functio laesa) in combination with a positive wound culture.

As of 2009, patient and clinical characteristics are prospectively registered in the Dutch Burn Repository (DBR) R3 in the three Dutch burn centres. Clinical outcomes that will be obtained from DBR R3 are mortality (during admission), time to first excision and grafting, length of hospital stay, length of ICU stay, readmission, reoperation, blood transfusion requirements, wound complications (e.g. graft failure), sepsis, shock, reconstructive surgery, number and timing of outpatient visits. To assess the amount of clinical topical wound treatments, the length of hospital stay will be used as a proxy.

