#### Patient and treatment characteristics

Demographics, burn characteristics, and treatment characteristics will be obtained from DBR R3.

Demographics: age, gender, medical history, referral, burn centre. Burn characteristics: TBSA, date of burn injury, burn localisation, burn aetiology, inhalation injury. Treatment characteristics: date of initial surgical intervention and thereby time till first surgical intervention (in days), admission on Intensive Care Unit (ICU), ventilation, topical wound treatments, and wound debridement method, type of grafting, other surgical interventions if applicable.

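### Treatment group is assigned per patient, but scar quality, healing and infection are measured per study area, and no named surgery timing is tied to that area

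*Protocol article*

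**What the plan says.** **Exposure is per patient.** Study design states "Depending on the received treatment, patients will be categorized as either the conservative treatment group" or the early excision and grafting group. Selection repeats it: "The used treatment strategy determines to which group the patient is assigned".

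**Key outcomes are per wound.** Burn wound area selection allows up to two qualifying burns per patient. Under Scar quality, "two independent observers assess the Observer Scale on the study area(s", and Clinical outcomes defines both wound healing and wound infection for the study area(s).

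**Mixed depth is admitted.** Criteria accepts a "mixed blue and yellow wound area on LDI" if a demarcated, mainly yellow part measures at least 25 cm². No limit is set on full-thickness burns elsewhere. Of full-thickness burns the Introduction says "No spontaneous healing is expected and excision and grafting are always indicated".

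**Surgery timing.** Clinical outcomes lists "time to first excision and grafting" among the items taken from the burn registry (DBR R3). Patient and treatment characteristics lists the registry's date of initial surgical intervention and the time derived from it. Neither carries the study-area qualifier given to healing and infection. Statistical analysis treats time to surgical intervention as a time-to-event outcome.

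**The concern.** The comparison needs to know how the scored piece of skin was treated. The article instead attaches treatment to the patient, and its own entry criteria admit patients in whom the two can differ. Two situations matter:

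- **Surgery outside the study area.** A full-thickness area is excised early while the yellow study area is dressed and heals, or is grafted late. If the patient is called early because of the first operation, a conservatively treated area is scored under early excision.
- **Two study areas treated differently.** One is grafted early and the other conservatively. Whichever label the patient gets, one area is in the wrong group.

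At stake is the primary contrast in scar quality, together with healing and infection of the study area. The Discussion says the results will feed a decision aid and a cost-effectiveness study. Time to surgery has a related problem: as named, it can be the time to an operation on a burn that is not being followed.

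**Working it through.** The plan has no figure to reproduce here. The Sample size section gives a forecast of at most 204 patients without a formal calculation, and the counts behind it are not shown. The main check is of the text.

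**Step 1: units side by side**

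| Item | Unit in the article | Section |
|---|---|---|
| Treatment group | patient | Study design; Selection |
| POSAS Observer Scale | study area, up to two | Scar quality; Burn wound area selection |
| Healing, infection | study area | Clinical outcomes |
| Time to first excision and grafting; date of initial surgery | not tied to the study area | Clinical outcomes; Patient and treatment characteristics |
| Length of stay, quality of life, return to work | patient | Clinical outcomes; Patient reported outcomes |

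Row 1 matches the last row but not rows 2 and 3.

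**Step 2: can the units diverge within the entry criteria?** Yes. Blue and yellow burns are eligible, full-thickness skin is always operated on, and two areas may be followed. The Introduction does not say when full-thickness skin is excised, so how often this happens in the early window is unknown.

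**Step 3: what a wrong label would do.** Let m be the share of the early-labelled group whose study area was in fact treated conservatively. Let D be the true early-minus-conservative difference in mean POSAS. Let s be the amount by which the mislabelled patients' mean score exceeds that of the conservative group, for example because their burns are deeper. Then

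observed difference = (1 − m)·D + m·s.

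If s = 0, this is simple dilution to (1 − m)·D. For scale only, I assume 102 per group (204/2), SD 1, two-sided alpha 0.05, and power = Φ(|observed|·√(102/2) − 1.96):

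| m | Power, D = 0.4 | Power, D = 0.5 |
|---|---|---|
| 0 | 81.5% | 94.6% |
| 0.05 | 77.5% | 92.4% |
| 0.10 | 72.9% | 89.5% |
| 0.20 | 62.8% | 81.5% |
| 0.30 | 51.6% | 70.5% |

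If s is not 0, the direction depends on the sign of D. Take m = 0.20 and an assumed s = 0.5 (higher POSAS is worse):

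- Early better, D = −0.4: 0.8 × (−0.4) + 0.2 × 0.5 = −0.32 + 0.10 = −0.22. The benefit is nearly halved.
- Early worse, D = +0.4: 0.8 × 0.4 + 0.2 × 0.5 = 0.32 + 0.10 = +0.42. The difference is slightly enlarged.

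The documents give none of m, D, s, the SD, alpha or the group split. The dilution table is therefore one case among several and is not an estimate for this study.

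**The case against.** A reader might infer that patients are grouped by the registry's first surgery date and that those with another burn excised early are therefore misclassified. The article does not support this. It groups by treatment received or strategy used, and lists the registry timings only as an outcome and a treatment characteristic. The Procedures section describes both strategies as treatment of the burn, and the Discussion says the followed burns are all deep partial-thickness. On a natural reading, then, treatment received may mean treatment of the followed burn, and excising a separate full-thickness area would not count as early excision. The full protocol or analysis plan, not shown, may say so. This stands: misclassification in the first situation is possible, not established.

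A reader might also infer that the error would push the result towards no difference. That holds only if mislabelled patients score like the conservative group. They probably have deeper or more extensive burns, so the direction is open. The planned regression on patient, burn and centre characteristics, with TBSA collected, may reduce the severity component, but it cannot correct a wrong exposure label.

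One part survives even the reading most favourable to the plan. If treatment received means treatment of the followed burn, a patient with two followed burns treated differently still cannot be given one correct label. This follows from the rule as stated.

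**Conclusion.** The point holds as a mismatch of units. The stated rule gives one label per patient, while the primary outcome and two secondary outcomes are scored on up to two areas per patient. The rule fails for patients with two differently treated areas, and it is ambiguous for patients operated on outside the study area. As named, time to surgery can refer to a different burn.

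The size cannot be derived from the documents. Patients with only yellow burns, all treated alike, are unaffected. If 10% to 30% of the early group were mislabelled and scored like the conservative group, the contrast would shrink by the same 10% to 30%. With a severity difference it could shrink further or grow. The gap should be closed before the primary comparison is run, but the documents do not show that the planned result is already biased, or in which direction.

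**What to change.** - **Exposure for study-area outcomes.** State that, for POSAS on the study area, healing and infection, the group is determined by the treatment that the study area itself received, whatever was done to other burns.
- **Data.** Record in Castor, from existing operative notes, whether each study area was excised and grafted and on what date, or that it was never grafted. Use this for grouping and for time to surgery in place of a patient-level first date.
- **Two areas in one patient.** Keep each under its own exposure, and analyse with a patient-level random effect or cluster-robust standard errors. Statistical analysis currently names a multilevel model only for categorical outcomes.
- **Surgery at 10–14 days.** Keep these areas identifiable, since Statistical analysis foresees exploring that group. They should not fall silently into the conservative group.
- **Patient-level outcomes.** For length of stay, quality of life and return to work, state a patient-level grouping rule. Set patients whose areas were treated differently apart in a sensitivity analysis.
- **Reporting.** Give the number of patients whose study area was treated differently from another burn or from the second study area, so that the share now unknown becomes visible.

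Cost: one date and one yes/no field per area, at most two areas per patient, and a slightly more complex model. No extra visits or patients are needed.

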### Protocol and registration

This protocol is in accordance to the Standard Protocol Items: Recommendations for Interventional Trials (SPIRIT) guidelines [22]. The SPIRIT Figure and SPIRIT Checklist are given in Fig 1 and S1 File.

**Fig 1 pone.0299809.g001:**
[figure not shown]
SPIRIT schedule of enrolments, interventions, and assessments.

### Participants

#### Selection

Neither, randomisation nor blinding will take place. The used treatment strategy determines to which group the patient is assigned. The first group represents conservative treatment with delayed excision and grafting if needed, the second group represents early excision and grafting. If a patient is eligible for the study, a member of the research team will provide information about the study. The patient is asked for consent to take additional measurements 12 months after discharge. After reflection time and written informed consent, the patient is included.

Anyone using the protocol must consider the ethical implications of the timing of surgery in their own practice setting. To ensure patient safety, the attending physician is justified in deciding not to start or discontinue treatment from the allocated treatment, based on sound medical grounds and after consulting with the health care team. Deviation from the assigned treatment should be rare, and the reason must be thoroughly documented.

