### Ethical considerations and declarations

In consultation with the medical ethics committee, it was agreed that the treatment strategies are part of usual care. Therefore, a medical ethics request was made solely for the conduction of the POSAS 12 months after discharge. The Medical research Ethics Committees United (MEC-U) has confirmed that the Medical Research Involving Human Subjects Act (WMO) does not apply to this study (W23.039) on March 14^th^ 2023. The study protocol was approved by the local review boards of all participating hospitals: Maasstad Hospital Rotterdam (L2023027), Red Cross Hospital Beverwijk (23.010), and Martini Hospital Groningen (2023–080).

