### Study status and timeline

Data collection from DBR R3 and BORN started on July 15^th^ 2022. Inclusion of participants started after approval of the local review boards of all participating hospitals on June 25^th^ 2023. The first patient inclusion and 12-month POSAS was conducted on June 30^th^ 2023. Data collection and participant selection is expected to be completed in January 2025.

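### Inclusion rests only on consent to the 12-month measurement, so if the rule is applied as written, first-period in-hospital deaths cannot be counted and the acute outcomes describe consenting survivors

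*Protocol article*

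**What the plan says.** All references are to the protocol article.

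- **Selection** gives one entry rule. "The patient is asked for consent to take additional measurements 12 months after discharge", and then: "After reflection time and written informed consent, the patient is included". No second population is described.
- **Study design** sets the two periods. "The first nine-month period (July 15^th^ 2022 to April 14^th^ 2023) this strategy is followed", and "In the following nine-month period (April 15^th^ 2023 to January 14^th^ 2024) clinical practice will be changed". The same section assigns patients to the compared groups by the treatment they received, not by period.
- **Study status and timeline** dates the opening of inclusion: "Inclusion of participants started after approval of the local review boards of all participating hospitals on June 25^th^ 2023". It adds: "The first patient inclusion and 12-month POSAS was conducted on June 30^th^ 2023". Registry data collection is dated separately, from 15 July 2022.
- **Clinical outcomes** begins its registry list with "Clinical outcomes that will be obtained from DBR R3 are mortality (during admission". The list goes on to ICU stay, readmission, transfusion, sepsis and shock, among others.
- **Statistical analysis** applies the same family of two-group tests to scar quality and to the other outcomes, and names no separate analysis set for the registry outcomes.
- **Ethical considerations and declarations** treats both strategies as usual care and says that "a medical ethics request was made solely for the conduction of the POSAS 12 months after discharge".

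**The concern.** An outcome that can occur only during admission is paired with an entry condition that, for first-period patients, could be met only weeks to months later. A patient must have survived the admission, been reachable and agreed to a late visit before counting as included. If the acute outcomes are taken from that set, deaths are missing from it, and so are the ICU days, sepsis, shock and transfusions of those who died. Patients with a hard course who survive but decline or cannot be traced are missing too.

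The Discussion sends the study's results to a decision aid and a cost-effectiveness study. Mortality and complication figures that silently describe consenting survivors would mislead both. The 12-month scar score is not the issue here, since it can only be measured in survivors who attend.

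**Working it through.** **Inputs from the article**
- Period 1: 15 July 2022 to 14 April 2023 (Study design).
- Period 2: 15 April 2023 to 14 January 2024, which is 275 days (Study design).
- Inclusion opened 25 June 2023; first inclusion 30 June 2023 (Study status and timeline).
- Expected number: at most 204 patients (Sample size). This is a feasibility count from registry and trial data whose figures are not given, so it cannot be reproduced. It is used below only for scale.
- No mortality rate, consent rate or split by period is given.

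**Step 1: delay before a first-period patient could be included**
- From the last day of period 1 to the opening: 16 days left in April + 31 in May + 25 in June = 72 days.
- From the first day of period 1 to the opening: 345 days.
- To the first actual inclusion, five days later: 77 and 350 days.

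Every first-period inclusion is therefore retrospective by at least 72 days from the burn. A first-period in-hospital death could enter the included set only if the patient was still an inpatient on or after 25 June 2023, consented, and then died in that same admission. That is possible in principle but negligible in practice.

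**Step 2: the second period**
- Days before the opening: 15 April to 24 June = 16 + 31 + 24 = 71 of 275 (26%).
- Remaining days: 275 − 71 = 204 (74%). That this equals the expected number of patients is coincidence.

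Two readings are open, because the article does not say when second-period patients are asked:
- *A. Asked in hospital once inclusion was open.* Death after consent is possible for about 74% of the period, so survivor selection differs between periods.
- *B. Asked around the 12-month visit.* Deaths vanish from both periods and the mortality comparison is empty. The pairing of the first inclusion with a 12-month POSAS, and the expected end of participant selection in January 2025, fit this reading.

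**Step 3: scale, under assumptions**

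Assume a true in-hospital mortality *m*, equal in both periods, and 204 / 2 = 102 eligible patients per period. Expected deaths = 102*m*. Chance of a genuine zero = (1 − *m*)^102. Under reading A, the second-period rate visible among included patients is at most about 0.742*m* (204/275 = 0.742), ignoring patients burned before the opening who were still in hospital after it.

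| Assumed *m* | Expected deaths per 102 | Chance of a genuine zero | Included set, period 1 | Included set, period 2 (A, at most about) | Included set, period 2 (B) |
|---|---|---|---|---|---|
| 1% | 1.0 | 0.36 | about 0 | 0.7% | about 0 |
| 2% | 2.0 | 0.13 | about 0 | 1.5% | about 0 |
| 5% | 5.1 | 0.005 | about 0 | 3.7% | about 0 |

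**Step 4: from periods to compared groups**

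The comparison is by treatment received. Early surgery was allowed in period 1 and conservative treatment in period 2, and the article gives no crossover figures. The period-1 zero therefore carries into the groups only in part, and the resulting bias between them cannot be calculated.

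**The case against.** The strongest reply is that no section says the registry outcomes are restricted to consenters. Consent is sought only for the additional 12-month measurement, the ethics request covered only that measurement, and the mortality data come from a registry running in all three centres since 2009. The timeline dates registry collection almost a year before inclusion. All of this fits an analysis of every eligible patient. Under reading B, listing in-hospital mortality makes sense only if that is what is intended. One may add that analysis sets are commonly left to an analysis plan.

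Much of this stands, and it rules out three stronger readings that a reader might infer:
- *That first-period mortality is zero by construction, as a fact.* It is practically zero among included patients; whether they are the analysis set for registry outcomes is not stated.
- *That one compared group can have no deaths.* Groups follow treatment received, so a second-period patient treated conservatively who consented and then died would count in the conservative group.
- *That the bias works against early surgery.* Second-period conservative patients are selected on clinical judgement, and their deaths would count the other way. Recruitment in hospital late in period 2 is itself an inference.

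What does not stand is that this is merely detail for an analysis plan. Who is in the study is a protocol matter, and the only rule given conflicts with a listed outcome. The rule is written for the study as a whole, not for a scar substudy. The exclusion of patients unable to complete the POSAS applies to the whole study, there is one expected sample, and one set of tests serves all outcomes. If all eligible patients are meant, the Selection section says something else.

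**Conclusion.** The point holds conditionally. If the inclusion rule is applied as written, first-period in-hospital deaths are essentially uncountable, and the acute outcomes describe survivors who agreed to a late visit. About 1 to 5 deaths per period is the scale of what would be lost, resting wholly on an assumed risk of 1% to 5% and an assumed even split of the maximum 204. The size and direction of any bias between the treatment-received groups are unknown. If second-period patients were also included around 12 months, the mortality comparison is empty in both groups.

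The primary scar outcome is outside this point. The article's own ethics and timeline sections suggest that the registry outcomes need not depend on this consent, so the conflict can be repaired.

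**What to change.** Amend the Selection section to define two populations, and refer to them in the Clinical outcomes and Statistical analysis sections.

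1. **Registry outcomes** (in-hospital mortality and all others taken from DBR R3): every eligible patient with a burn from 15 July 2022 to 14 January 2024, whether or not the patient consents to the 12-month POSAS, subject to confirmation by the local boards.
2. **12-month POSAS**: the consented subset only.
3. **Reporting**: numbers eligible, deceased and non-consenting, by period and by treatment group.

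If registry data may not be used without this consent, remove mortality from the compared outcomes and state that the remaining acute outcomes apply to consenting survivors.

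The cost is a change of wording, one registry extract over dates that data collection already covers, and possibly a confirmation from the local boards.
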